## Discussion

The current study presents a controlled intervention involving personalized sleep and nutritional strategies for shift workers in a real-world setting. Previous studies have demonstrated a promising role for modifiable behavior in the prevention of disrupted sleep or glucose regulation in night shift workers [20, 23]. Despite these earlier studies, a notable gap still exists in our understanding of the effectiveness and long-term effect of these interventions in real-life settings.

The controlled design and comprehensive approach of this study will offer valuable insights into the multifaceted challenges encountered by shift workers. This encompasses the complexities of managing health and sleep amidst the demands of night shifts and individual and familial responsibilities. The findings of the GRIP study may serve as a foundation for refining and expanding interventions. For instance, if the findings indicate that adjusting the timing of food intake is both feasible and effective in mitigating negative health consequences, these findings could catalyze widespread adoption of interventions that target these modifiable behaviors. Furthermore, the identification of biomarkers linked to long-term circadian disturbance may be an important asset in monitoring the effects of such interventions.

In summary, this research deploys an array of biomarkers and wearable technology to examine the role of the circadian system in disease prevention for night shift workers, thus offering a unique contribution to the field of study. Understanding how personalized interventions impact the sleep and health of actual shift workers is not only essential for bridging knowledge gaps but also for crafting practical solutions that can potentially result in improved health, decreased healthcare expenses, and increased sustainable employability.

### Strengths & limitations

The first strength of this intervention is its diverse set of biomarkers, including markers of long-term health. In combination with the 1-year follow-up, this allows for an integrated view of altered physiological processes and contributes to the limited research on prevention of long-term health effects of shift work. Second, the intervention takes place in a real-life context. This enables us to explore the feasibility of the intervention within a day-to-day setting, as well as capture a high quality exposure assessment. With wearable devices such as the actigraphy watch and CGM, we can collect continuous objective data and combine this with actual information on worked shifts and food consumed. Especially the less-explored continuous processes are relevant, as they may provide a more concrete understanding of the underlying dynamics. Lastly, within the repeated measurements design participants can serve as their own controls, increasing the sensitivity of the analysis to potentially smaller changes.

Despite the strengths of this approach, there are potential pitfalls. First, participants will have the opportunity to select their preferred intervention. The researchers are aware that participants’ preferences might introduce a small confounding or selection bias to the data. However, the estimated risk for bias is judged to be low, as expected/putative confounding domains (i.e. chronotype, diet quality, activity level) will be measured validly and reliably and will be carefully controlled in the analysis. Moreover, the approach of individual preference might increase adherence and positive outcomes for participants. Indeed, allowing participants to select their preferred intervention, has been associated with beneficial outcomes, via an increased sense of autonomy within occupational health [63]. Furthermore, in the health promotion field, interventions that permit participants to select their preferred program consistently deliver the best outcomes in terms of health risk reduction, and are considered “best practice” [64]. Second, factors outside the scope of the study, such as workplace policies, personal lifestyle changes, or other external influences, might affect the results but could be challenging to account for. However, by inquiring about changes in the personal sphere or workplace at the follow-up meetings we expect to capture these external factors as well as possible, so that they may be estimated in our analysis. Third, during the course of the study, the changing of seasons could influence the circadian rhythm [65] of the participants due to variations in natural light exposure, temperature, and overall environmental conditions associated with different seasons. To mitigate this, careful consideration of seasonal changes (not only in the intervention groups but also in the control group) will be included in the results and their interpretation. Lastly, the inclusion of only male participants in our study hinders the generalizability to female nightshift workers.

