## Methods

### Study design

A non-blinded controlled intervention study will be used to investigate the effect of a personalized sleep or nutritional intervention. The study will include a run-in period with baseline levels, a 3-month intervention with measurements at the start of the intervention, post-intervention measurements immediately following the intervention, and a follow-up after 12 months. There are three study arms: control group (no advice), personalized sleep intervention (SL), and personalized nutritional intervention (NU). During the run-in period the following will be measured: sleep, physical activity, food intake, and glucose levels by continuous glucose monitoring (CGM) during 14 days covering night shifts, rest days, and non-night shifts. Information from this baseline will be used for the subsequent personalized advice. The intervention entails following the personalized advice for a period of three months.

The groups will be open-labeled. The intervention involves observable behavioral changes, of which the participants will be aware themselves. This makes it difficult to conceal whether a participant is receiving the intervention or not. Participants will have the opportunity to select their preferred intervention. This approach was chosen to optimize motivation for participants to adhere to the personalized intervention.

The study has been approved by the Medical Ethical Review Committee of the Erasmus University Medical Center (Erasmus MC) and registered (27 November 2023) under ClinicalTrials.gov identifier NCT06147089. Participant recruitment is ongoing at the time of submission. An overview of the study setup is depicted in Fig. 1.

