### Study population

The study population will consist of male employees who work at least 4 night shifts a month on average, with at least 1 year prior experience with shift work. Participants work in shifts with a duration of 6 h-12 h. A shift is categorized as a night shift if at least 1 h of working falls between midnight (00:00) and 06:00 in the morning. Participants can work night shifts only or work on rotating shifts. Participants are 18 to 60 years of age and without a diagnosis of a major disease. All participants live or work in the Netherlands and speak Dutch natively or fluently. The aim is to include 25 participants in each arm of the study.

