### Statistical analysis

Our primary analysis will assess the changes over time (pre- and post-intervention) in sleep quantity, sleep quality and glucose regulation. The intra-individual differences within the NU and the SL group will be compared to the control group. By considering the intra-individual differences, participants can serve as their own controls, increasing the sensitivity of the analysis to potentially smaller changes.

Linear and logistic mixed models will be employed using statistical software (SPSS, R studio) to analyze the main effects over time for the factor condition (3 groups). A random intercept statement will account for inter-individual variations. Significance tests will be 2-tailed and at p ≤ 0.05. Covariates like age, sex, and BMI may be considered, and participants with baseline and at least one follow-up measurement will be included in the statistical analyses. Selective loss to follow-up will be analyzed through logistic regression. Covariates will be imputed using multiple imputation if needed.

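### The article names season as an influence but commits to no calendar term in the model, so any difference in enrolment timing between the self-chosen arms would bias the T0–T2 contrast

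*Protocol article*

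**What the plan says.** Strengths & limitations lists three time- or selection-related pitfalls and treats them differently.

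- **Self-selection.** The confounders named there (chronotype, diet quality, activity level) "will be carefully controlled in the analysis". Season is not among them.
- **External changes at work or home.** These are asked about "so that they may be estimated in our analysis".
- **Season.** The article accepts that "the changing of seasons could influence the circadian rhythm" through light, temperature and other conditions. The mitigation is that "careful consideration of seasonal changes (not only in the intervention groups but also in the control group) will be included in the results and their" (the sentence ends on interpretation).

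Statistical analysis describes mixed models with a random intercept and compares within-person change in each intervention arm with change in control. On adjustment it says "Covariates like age, sex, and BMI may be considered". No calendar or day-length term is named.

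On how the arms are formed, Study design says "Participants will have the opportunity to select their preferred intervention", and Study population says "The aim is to include 25 participants in each arm of the study". No section describes enrolling the arms in parallel or balancing them over the year. The sequence in Study design is run-in, a three-month intervention, then post-intervention measurement, so T0 and T2 are at least three months apart.

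**The concern.** Season varies within a person, so using participants as their own controls does not remove it. Nor does adjustment for baseline age, BMI or chronotype. Only the comparison with the control arm can remove it, and only when the arms are measured over similar calendar months. Randomisation would make that likely. Allocation by preference does not, and nothing else in the article secures it.

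If the sleep or nutrition arm happens to start at a different time of year from control, the difference in seasonal change is added to the estimated intervention effect on total sleep time (TST) or glucose. It can create an effect or hide one. Considering season when results are discussed does not take that component out of the estimate; a term in the model can. The 12-month follow-up gives no same-season check for the device outcomes, because actigraphy and continuous glucose monitoring are scheduled at T0, T1 and T2 only.

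**Working it through.** **1. The plan's own figure.** Inputs from Sample size calculations: glucose SD 0.49 mmol/L, correlations 0.85 (T0–T1) and 0.71 (T1–T2), difference 0.23 mmol/L, alpha 0.05, power 0.80. The T0–T2 correlation is not given; I assume 0.71. I take two groups, with the difference present at T1 and T2, and the Hotelling-Lawley test.

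In units of SD², the contrasts T0−T1 and T1−T2 have variances 2(1−0.85) = 0.30 and 2(1−0.71) = 0.58, and covariance 0.85−0.71−1+0.71 = −0.15. The determinant is 0.30×0.58 − 0.15² = 0.1515. The noncentrality is λ = (n/2) × (0.23/0.49)² × 0.58/0.1515. At n = 25 this is 12.5 × 0.2203 × 3.828 = 10.54 on 2 and 2n−3 = 47 df. Power is 0.811 (0.792 at n = 24), so 25 per group is reproduced.

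**2. Seasonal change within one person.** Assume a yearly sinusoid with peak-to-trough swing S. The largest change over 90 days is S × sin(π×90/365) = 0.70 S. Many start dates give less: for a three-month interval, about 23% give a change below 0.25 S and about 11% below 0.125 S.

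**3. Bias in the contrast with control.** Let d be the difference between two arms in the share starting at the date of greatest rise rather than greatest fall. Then bias = d × 2 × 0.70 S = 1.40 d S.

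- d = 0 (concurrent enrolment): 0
- d = 0.20: 0.28 S
- d = 0.40: 0.56 S

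**4. Illustration.** S is not in the article; these values are assumptions.

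| Outcome | Assumed S | Bias, d = 0.20 | Bias, d = 0.40 | Share of planned difference |
|---|---|---|---|---|
| TST (planned 128 min) | 20 min | 5.6 min | 11.2 min | 4–9% |
| TST | 40 min | 11.2 min | 22.4 min | 9–18% |
| Glucose (planned 0.23 mmol/L) | 0.1 mmol/L | 0.028 | 0.056 | 12–24% |
| Glucose | 0.2 mmol/L | 0.056 | 0.112 | 24–49% |

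**5. Sensitivity to the setup.** With a four-month interval the largest within-person change is S × sin(π×4/12) = 0.87 S, and the two biases become 0.35 S and 0.69 S. If instead whole arms were displaced by 1, 2 or 3 months, the worst case at a three-month interval is 0.37 S, 0.71 S or 1.00 S. That pattern requires everyone in an arm to start on one date, so it is a bound and not a forecast.

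**6. Cost of adjusting.** Two seasonal terms reduce the denominator df from 47 to 45, and glucose power goes from 0.811 to 0.809 if the arms are season-balanced. If season explains a share R² of arm membership (assumed), approximate the loss by multiplying λ by 1−R²:

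| R² | λ | Power |
|---|---|---|
| 0.10 | 9.49 | 0.764 |
| 0.25 | 7.91 | 0.681 |
| 0.40 | 6.33 | 0.578 |

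**The case against.** The strongest reply is that this is an article. Its covariate list is open, a fuller analysis plan may already contain a season term, and including season in the results could mean an adjusted analysis. A reader might therefore infer too much by saying that season is left to narrative discussion alone; the text refers to the results as well as their interpretation. That stands. What remains is that the article does state a mitigation, that its wording is weaker than the commitments made beside it for the other two pitfalls, and that it names no method.

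Three further inferences are tempting and are not supported.

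- **That every pre/post comparison spans a change of season.** T3 is 12 months after baseline, T1 is at the start of the intervention, and some T0–T2 windows straddle a seasonal turning point with little net change.
- **That arms are capped at 25, so the popular one fills first and latecomers take what is left.** The article gives 25 as an aim, and says participants choose. Staggered filling is possible but not described.
- **That a seasonal shift is in itself a flaw in the contrast.** A shift common to all arms cancels against control.

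The size is also open to challenge. S, the sinusoid and the degree of imbalance are all assumed, and the calculation puts starts at the extreme dates. The article gives no seasonal effect on sleep time or glucose.

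**Conclusion.** The point holds as a conditional one. The article recognises a time-varying influence, compares non-randomised arms on change over at least three months, and commits to neither a calendar term nor calendar balance. Any difference between arms in enrolment timing would therefore bias the primary T0–T2 contrast. With concurrent enrolment the bias is zero, and the article does not show that timing will differ.

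The magnitude cannot be taken from the document. Under the sinusoid, a 90-day interval and extreme start dates, an imbalance of 20 to 40 points gives at most about 0.28 S to 0.56 S. For the swings assumed above, that is minor against the planned sleep difference and could be material against the planned glucose difference. It would be wrong to conclude that the trial's results will be seasonally biased. The supported conclusion is that the stated handling cannot remove such a bias if it arises, whereas a model term built from measurement dates can.

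**What to change.** In Statistical analysis, state that the mixed models for the sleep and glucose outcomes include a time-varying seasonal covariate: day length at the mid-date of each 14-day measurement window, or the sine and cosine of that calendar date. If the sponsor prefers to keep the primary model without it, pre-specify the season-adjusted model as an analysis reported beside it. Report the number of participants starting in each calendar month by arm, and align the season sentence in Strengths & limitations with this.

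The covariate needs only the dates of the measurement windows. It costs one degree of freedom for day length or two for sine and cosine, which is negligible when the arms are season-balanced. If season and arm are correlated, the cost is a real loss of precision, shown in step 6 of the working. That loss would reflect how little the data can separate season from intervention, and the start-month table lets readers see it.

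Releasing places per arm in calendar blocks would address the same risk, but it would restrict the free choice that Study design adopts to support motivation. That is a trade-off for the sponsor and not part of this recommendation.

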## Conclusion

This study aims to improve sleep and metabolic health in night workers by introducing a personalized sleep or personalized nutritional intervention. The interventions are directed at alleviating both behavioral and physiological contributors to circadian rhythms and consequently minimizing health risks. Sleep, glucose regulation, biomarkers, and general health parameters will be evaluated. This study is unique in its personalized character, extensive combination of objective and subjective measurements and its long follow-up. This study will contribute to the current need for preventative health measures for night shift work in a real-life context.

## Data Availability

No datasets were generated or analysed during the current study.

## Abbreviations

EU: European Union
SL: Personalized sleep intervention
NU: Personalized nutritional intervention
CGM: Continuous glucose monitor
TST: Total sleep time
ISI: Insomnia severity index
ESS: Epworth sleepiness scale
PSQI: Pittsburgh sleep quality Index
SWD: Shift work disorder
CHO: Carbohydrates
PRO: Protein
F: Fat
FI: Fragmentation index
WASO: Wake after sleep onset
CTI: Circadian type inventory
FFA: Free fatty acids
TG: Triglyceride
TNF-α: Tumor necrosis factor alpha
PVT: Psychomotor vigilance test
RT: Reaction time
KSS: Karolinska sleepiness scale
VAS: Visual analogue scale
PSS: Perceived stress scale
CV: Coefficient of variation
MAGE: Mean amplitude of glycemic excursions
MODD: Mean of daily differences
HDL: High-density lipoprotein
LDL: Low-density lipoprotein
hs-CRP: High sensitive C-reactive protein
IFN-γ: Interferon gamma
IL: Interleukin
IP-10: Interferon gamma-induced protein 10
eGFR: Glomerular filtration rate
ASAT: Aspartate aminotransferase
ALAT: Alanine aminotransferase
gGT: Gamma-glutamyl transferase
Hb: Hemoglobin
Ht: Hematocrit
MCV: Mean corpuscular volume
